### Randomization

In order to control contamination and to limit interaction between the different groups, randomisation will be done on a cluster level. We aim to have 24 clusters (8 clusters per arm), 10 at Intrum and 14 at ICA-gruppen. Clusters will be composed while considering: 1) having a team or line manager, 2) having regular group meetings, 3) limited regular meetings with other teams. Block randomisation and assignment will be performed using a computer-generated random number list. Groups will be randomly allocated (1:1) with stratification for company and cluster size (large vs small). In order to implement the interventions in an order consistent with logistical capacity matched randomization will be used in case needed. Randomization will be performed after finishing first data collection and participants will be notified by email. Randomization and allocation will be performed by researchers not involved in data collection. Research assistants involved in data collection and processing will be blinded for group allocation.

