### Sample size

Sample size was calculated in three steps [67]:i.Sample size based on an individualized randomized controlled trialii.Corrected for the design effect, taking into account the clusteringiii.Corrected for unavailable data

The sample size calculation was based on 1 follow-up measurement, with a power of 80% and significance level of 0.05, corrected for 3 groups (0.05/3 = 0.017).

The design effect was 1.77. This was determined, assuming that the proportion of variance accounted for by between cluster variations was 0.05 [68]. Furthermore, we corrected for unequal clusters, assuming an average cluster size of 14 with a standard deviation of 5.83.

Unavailable data were assumed by correcting for the drop out of 3 clusters, with an average cluster size of 14 per group and for unavailability of data (missing, individual drop-outs) for 20% of participants.

For the remaining input of the sample size calculations, data were used from subproject 1 of the larger research project (as described earlier).

Using these input, estimated needed sample sizes are the following:Physical activity, moderate to vigorous physical activity, meeting the guidelines

Proportion of participants meeting guidelines in control group: 30%.

Estimated proportion of participants meeting guidelines in intervention groups: 60%.i.*Sample size based on individualized randomization:* 52 per groupii.*Corrected for design effect:* 92 per groupiii.*Corrected for unavailable data:* 125 per groupSedentary behavior, total sedentary behavior, in hrs/day

Difference in mean value between groups: 1 h/day.

Standard deviation: 1.4 h/day.i.*Sample size based on individualized randomization:* 41 per groupii.*Corrected for design effect:* 72 per groupiii.*Corrected for unavailable data:* 101 per groupMental health, stress, single item [24]

Proportion of participants with stress complaints in control group: 26%.

Estimated proportion of participants with stress complaints in intervention groups: 5%.i.*Sample size based on individualized randomization:* 57 per groupii.*Corrected for design effect:* 100 per groupiii.*Corrected for unavailable data:* 134 per groupCognition, stroop test (in seconds)

Difference in mean value between groups: 7 s.

Standard deviation: 9.85 s.i.*Sample size based on individualized randomization:* 41 per groupii.*Corrected for design effect:* 73 per groupiii.*Corrected for unavailable data:* 102 per group

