### Statistical analyses

In accordance with the research questions, statistical analyses will be conducted to determine whether the groups differ in changes over time in proximal, distal as well as secondary outcomes. Statistical significance will be set at the 5% level (two-tailed). To adjust for company and clustering, analyses will be performed using multilevel modelling. The models will include allocated group (reference group = control group) and baseline values. Both crude models and models adjusted for potential confounders will be determined. Potential confounders will be defined a priori based on the findings from the larger research project. Separate models will be made for the different outcomes regarding physical activity, sedentary behavior, mental health and cognition. All analyses will be performed using both per protocol and intention to treat approaches, were intention to treat is defined as persons attending at least 3 out of 5 counselling sessions.

Moderator analysis will examine whether intervention effects differ across individual (e.g. age, gender and education). Mediator analyses will test whether individual and organizational factors, described under working mechanisms, mediated the intervention effects.

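### Randomisation is stratified by company and cluster size, but the stated analysis model leaves out the size stratum, so standard errors may be modestly too large

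*Protocol article*

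**What the plan says.** The Randomization section restricts the allocation of clusters by two factors: "Groups will be randomly allocated (1:1) with stratification for company and cluster size (large vs small". It plans few clusters: "We aim to have 24 clusters (8 clusters per arm), 10 at Intrum and 14 at ICA-gruppen". It also allows that "matched randomization will be used in case needed".

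The Statistical analyses section describes the model in two sentences: "To adjust for company and clustering, analyses will be performed using multilevel modelling", and "The models will include allocated group (reference group = control group) and baseline values". Crude and adjusted versions are both promised. The covariates of the adjusted version are not listed: "Potential confounders will be defined a priori based on the findings from the larger research project". Cluster size is not mentioned anywhere in that section. The text does not say whether company enters as a fixed covariate or as a random level.

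**The concern.** The usual principle is that the analysis should respect the restrictions placed on the randomisation. Stratifying by cluster size balances the arms on it, so differences between large and small teams contribute little to the true sampling error of a treatment contrast. A model without the factor still counts those differences as between-cluster noise. Its standard error then describes a less restricted design than the one used, and it is too large when size is prognostic. The consequences are wide intervals, large p-values and lost power, in a trial with 8 clusters per arm.

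The clause on potential confounders does not close the gap. Size might be chosen as a confounder, but the crude models would still omit it.

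A second, smaller matter is the coding of company. The wording can be read as making company a level of the multilevel model. Two companies cannot support a reliable variance component, so the text should exclude that reading.

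**Working it through.** **Inputs from the protocol article.** Sample size section: ICC 0.05; mean cluster size 14 (SD 5.83); sedentary-time SD 1.4 h/day; planned difference 1 h/day; "with a power of 80% and significance level of 0.05, corrected for 3 groups (0.05/3 = 0.017". Randomization section: 24 clusters, 8 per arm, 10 and 14 by company. Statistical analyses section: "Statistical significance will be set at the 5% level (two-tailed".

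**The plan's own figures.** The design effect is 1 + ((CV² + 1)·m − 1)·ICC with CV = 5.83/14 = 0.416. This gives 1 + (1.1734 × 14 − 1) × 0.05 = 1.771 (stated 1.77). For sedentary time, 2 × (2.387 + 0.842)² × 1.4² = 40.9, or 41 per group as stated. Neither calculation takes credit for stratification, so nothing here depends on the analysis covariates.

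**Analytic check of the standard error.** The total variance is 1.4² = 1.96.
- Between-cluster variance: 0.05 × 1.96 = 0.098.
- Within-cluster variance: 0.95 × 1.96 = 1.862.
- Variance of a cluster mean at size 14: 0.098 + 1.862/14 = 0.231.
- Standard error of a contrast of 8 against 8 clusters: √(2 × 0.231/8) = 0.240 h/day.

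Suppose large and small teams differ by d, with half the clusters in each stratum. Leaving size out adds (d/2)² to the apparent cluster-mean variance. The documents give no d, so d is an assumption.
- d = 0: no inflation.
- d = 0.3: 0.15² = 0.0225, which is 23% of 0.098. The ratio of standard errors is √((0.231 + 0.0225)/0.231) = 1.048. If the 0.0225 is instead taken out of the 0.098, the ratio is √(0.231/0.2085) = 1.053. Either way the inflation is about 5%.
- d = 0.7: 0.35² = 0.1225. This exceeds the entire between-cluster variance of 0.098 that the protocol assumes, so it lies outside the plan's own inputs.

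**Simulation.** It used 24 clusters (10 + 14), half large and half small (sizes 19 and 9, assumed), permuted blocks of 3 within the four strata, SD 1.4, ICC 0.05 and weighted cluster-level regression. Each cell compares company only with company plus size.

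| Assumed size effect (h/day) | Mean model SE | Type I error | Power for an illustrative 0.5 h/day effect |
|---|---|---|---|
| 0 | 0.242 vs 0.243 | 5.0% vs 4.8% | – |
| 0.3 | 0.255 vs 0.243 | 4.1% vs 5.2% | 45% vs 48% |
| 0.7 (beyond the protocol's ICC) | 0.307 vs 0.244 | 1.9% vs 5.2% | 29% vs 46% |

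The mean estimate was unbiased in every model. The actual spread of the estimate hardly moved, at 0.259 vs 0.251 even for d = 0.7. What changes is the reported standard error.

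**At the planned effect of 1 h/day.** Take a true spread of 0.243 under both models and t critical values of 2.086 (20 df) and 2.093 (19 df). For d = 0.3, (1 − 2.086 × 0.255)/0.243 = 1.93 without size and (1 − 2.093 × 0.243)/0.243 = 2.02 with it. Power is about 97% and 98%. This assumes full clusters and testing at 5%. The 3-point loss therefore belongs to the smaller, illustrative effect.

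**Company random or fixed.** In a mixed-model check with 60 runs per setting, the treatment standard error was almost the same (0.250 vs 0.252; 0.302 vs 0.301). The random-company fit often failed to converge, and its company variance was about zero in 11 of 60 runs in one setting.

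**Degrees of freedom.** 24 clusters − 3 arms = 21. Company takes one and size takes one, leaving 19.

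**The case against.** The strongest reply is that covariate lists and the coding of factors commonly belong to the analysis plan, which is not shown, and that naming group and baseline does not exclude other terms. This has some force, and an analysis plan may already settle the matter. But the article is not silent. It names the factors it adjusts for, and that list contains one of its two stratification factors.

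Three stronger readings are tempting, and the documents do not support them.

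1. A reader might infer that the treatment effect is misstated. In a linear model it is not, because the estimate stays unbiased and any error in the reported precision is conservative. For the binary outcomes (meeting activity guidelines, stress complaints), the conditional odds ratio would shift somewhat with the covariate set. That is a change of estimand and was not quantified.

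2. A reader might infer that company is a random level, so that adjustment for it fails or costs precision. The text says company is adjusted for, and a multilevel model can hold it as a fixed effect. Even as a random level, the treatment standard error was practically unchanged. What stands is ambiguity and the risk of unstable fits.

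3. A reader might expect a larger loss. Supposing that company and size together explain 20–40% of between-cluster variance, which is 37–42% of the variance of a cluster mean, would suggest a 7–17% variance reduction. That share has no source in the documents, it credits company although company is already adjusted for, and it concerns reported rather than actual variance. The 26% inflation at 0.7 h/day (0.307/0.244) requires more between-cluster variance than the protocol assumes.

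It is also fair to say that baseline adjustment, which is planned, would absorb part of any stable size effect.

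**Conclusion.** The point holds as a mismatch between the stated randomisation and the stated model. Cluster size is a stratification factor, and it is absent from the named adjustment factors and model terms. The treatment estimate of a linear model is not biased by this. If size is prognostic, standard errors, intervals and p-values are conservative and some power is lost.

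The size of the problem is modest. It rests on an assumed large-versus-small difference of 0 to 0.3 h/day in sedentary time, with large and small clusters in equal numbers, SD 1.4 and ICC 0.05. Over that range the standard error is 0–5% too large, type I error goes from about 5% to about 4%, and power for a 0.5 h/day effect falls by up to about 3 points. The loss is smaller at the planned 1 h/day, and probably smaller again after baseline adjustment. The correction is still worth making because it costs almost nothing when size has no effect (0.242 vs 0.243).

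**What to change.** In the Statistical analyses section, and in the analysis plan if there is one:
- include the cluster-size stratum (large vs small), as used at randomisation, as a fixed effect in every model, including the crude one;
- state that company is a fixed effect;
- keep a random intercept for cluster (team).

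If matched randomisation is used, the same reasoning applies to the matching factor.

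The cost is a sentence of text. Both variables are known at randomisation, so no data collection changes. Size takes one cluster-level degree of freedom beyond the company adjustment already planned, making 2 of about 21 in total. No stated sample-size figure needs revision.

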### Interventions

Two multicomponent interventions of 6 months will be studied. The interventions are based on the ecological framework suggesting that behavior can be influenced on multiple levels including individual, social, organizational, environmental and policy [18]. In an ecological model proposed for sedentary behavior it has been further emphasized that in order to influence behavior, strategies should target multiple levels [19]. The taxonomy of behavior change techniques was used to translate theoretical components into intervention strategies, as well as to extract effective intervention components from other behavior change techniques and are descripted in Additional file 1 [20]. The exact content of the interventions has been defined by combining this framework with results from the first and second subproject of the research project [17], as well as having a continuous dialogue with both the involved companies about the intervention in all development stages.

When performing interventions to increase physical activity or reduce sedentary behavior in one context, there is a risk that people compensate by modifying their behavior in other contexts [21]. Therefore, the interventions will focus on both work- and leisure time.

The physical activity intervention aims to promote physical activity of moderate to vigorous intensity and includes:i.Individual: motivational counselling towards improving their time spent in moderate to vigorous physical activity, based on cognitive behavioral therapy (CBT) [22]. Including feedback on their moderate to vigorous physical activityii.Environmental: access to a commercial gym (6 months) as well as exercise sessions and lunch walks organized by team leaders and provision of company bikesiii.Organizational: team leaders encourage employees to be physically active during and outside working hours, including commuting to work

The sedentary behavior intervention aims to reduce sedentary behavior, including breaking up prolonged sitting and includes:i.Individual: motivational counselling towards reducing their time in sedentary behavior and breaking up prolonged sitting, based on CBT [22]. Including individual feedback on sedentary behaviourii.Environmental: implementation of standing and walking meetings, initiated by team leaders. Note that companies already provided their employees with sit-stand desks, however in the first part of the larger research project we found that usage of these desks to stand is limited [17]iii.Organizational: team leaders encourage employees to reduce sedentary behavior at work, both in meetings and while sitting behind their desk

#### Motivational counselling

This motivational counselling has a comparable design but a different focus in either intervention, respectively aiming at physical activity or sedentary behaviour. The counselling will be performed by professional health coaches from a health promotion company Itrim who will receive additional training on CBT techniques and on physical activity and sedentary behavior. These training sessions will last for two days and will be held by CBT educated psychologists and physical activity expert. All Itrim coaches have experience with behavior counselling and are used to face-to-face meetings with clients. In total there will be five sessions; three individual and two group sessions. The first individual session is scheduled to last 60 min, the other individual sessions 45 min, and group sessions 90 min. In between session one and two there will be two weeks and thereafter sessions are 4–5 weeks apart. After session three (in the middle of the active intervention period, approximate 3 months) the participants will be equipped with accelerometers and inclinometers to be worn for 7-days. At session four the participants will receive feedback of their physical activity or sedentary behavior (dependent on which group they are in) based on the assigned intervention. To standardize counselling sessions, coaches will get a checklist with multiple issues that they should address during the session and selected sessions will be recorded. The CBT techniques include 1) Goal setting tied to values and identifying the individual’s resources and boundaries for making behavior changes, 2) Functional analysis including antecedents and consequences of unwanted and wanted behavior, and 3) Acceptance techniques. The active components in the counselling according to the taxonomy of behavior change [20] is described in detail in Additional file 1.

#### Team leaders

The team leaders will play an important role in the delivery of the environmental and organisational components, which is described in detail in Additional file 2. Other important tasks are to encourage employees to participate and remain in the study and to communicate with the research team. Before the start of the study all team leaders will be invited to an information meeting to explain the project and their role in the project. At the start of the intervention all team leaders receive the relevant part (sedentary or physical activity dependent on randomization) of Additional file 2 and will be contacted by phone by one of the researchers to discuss a plan on how to implement the different components, which will be written down and confirmed by email. In case of changes or questions about the defined plans, the team leaders will be asked to contact the research team. After mid-term of the intervention period, the team leaders will be invited to an inspiring lecture and discussion with two experts on how to support behavioral changes. Within two months after the end of the intervention, team leaders will be contacted again by phone to evaluate the intervention. This is also part of a qualitative study planned to evaluate the feasibility of the intervention.

#### Waiting list

The waiting list control will be a passive control group that will be measured again after 6 months. After this measurement they will start the assigned randomized intervention.

### Data collection

Inclusion of the study will start in March 2018 and is planned to end in December 2018. Data of the randomized controlled trial is thus expected to be finished in May 2019 and the two year follow-up by the end of 2020. On all measurement occasions, participants will fill out web questionnaires and perform measurements at an in-house test site at the company. For a complete list of measurements, please see an overview in Additional file 3. This overview includes the specification of which measurements will be performed at which measurement time points.

#### Proximal outcomes: physical activity and sedentary behavior

Participants will be fitted with an Actigraph GT3X accelerometer on the hip during 7 days and on the non-dominant wrist during sleeping-time. Simultaneously, persons will be fitted with an inclinometer (ActivPal3 activity monitors, PAL technologies limited, Glasgow, UK) to measure sedentary behavior. The ActivPal is waterproofed and will be secured to the frontal aspect of the mid-thigh using a 10x10cm adhesive hypo allergic thin plastic film (Tegaderm Roll, 3 M). During the measurement period, participants will be given a diary in which they note sleep and waking times, working hours and any device removals.

#### Actigraph

The GT3X will sample 3-axial acceleration at a sampling frequency of 30 Hz. The accelerometer expresses intensity of movement in counts per minute (cpm). The triaxial acceleration vector magnitude (VM) will be calculated as, where x, y and z denotes the vertical, anteroposterior and mediolateral axes, respectively. Minimum requirement for data inclusion will be 600 min of valid daily monitor wear on at least 4 days. Wear time will be defined by subtracting non-wear time from waken time (as defined from the sleep diary). Non-wear time will be defined as at least 60 consecutive minutes with no movement (VM = 0 counts per minute, cpm), with allowance for maximum 2 min of activity.

Daily physical activity pattern will be presented as 1) percentage of wear time spent in three intensity-specific categories; sedentary, light and moderate-to vigorous physical activity, 2) total volume of physical activity expressed as mean cpm over the study period, 3) time spent in prolonged (> 20 min) periods spent sedentary, 4) number of breaks per sedentary hour, 5) fulfilment of national physical activity recommendations and 6) total physical activity.

#### ActivPAL

This inclinometer registers the inclination of the thigh to distinguish between sitting, standing and walking. The inclinometer will be initialized and processed using the activPAL software, using references from participants’ diaries on waking and working hours. Additional data processing will be performed with the HSC analysis program (developed by [name] and [name], School of Health and Life Sciences, Glasgow Caledonian University). Before and after processing, quality controls will be conducted and recorded time will be coded as wear time, non-wear time or working time. Sleep and non-wear time will be excluded. For a day to be considered valid the following rules will apply: 10 ≥ hours of worn waking hours, < 95% of time spent in any one behavior (sedentary, standing, walking) and ≥ 500 steps [23]. Working days will be considered valid when worn for ≥80% of the time at work and 5 ≥ hours of worn working hours. To be included in the analytical sample, data from at least four days is required, with at least two working days and two non-working days. Time spent sitting, standing and walking will be identified for each day and then averaged over the valid days. In addition, sitting bouts will be analysed. Distributions of activities will be reported separately for workplace, non-workplace, working days and non-working days. All results will be presented in hours/day and in % wear time.

#### Distal outcomes: mental health and cognition

##### Mental health

The following self-reported measures will be assessed: Stress [24], Recovery [25], Depression and anxiety [26], Burnout [27], General mental health [28], Well-being [29], Sickness absence [30], Life satisfaction [31], and Performance-based self-esteem [32].

